### Acceptability outcomes

The total number of interviews will depend on when data saturation is reached, i.e. when it is unlikely to lead to the identification of any significant new issue or novel insight. We hope to reach saturation with 18 in-depth interviews with heads of households and 10 focus group discussions with approximately 8 to 10 participants per group.

### Ancillary and post-trial care

As mentioned earlier, all families in homes participating in the study irrespective of whether they are in the control and intervention arm are enrolled in a health insurance scheme paid for by the study which assures free healthcare for the study duration. Furthermore, the study team assures that all study participants and their families receive the promised services free of cost. Not all healthcare providers working in institutions participating in the insurance scheme are yet fully aware of the operational aspects of the insurance scheme which has only recently been introduced in Tanzania. The free insurance coverage and free house maintenance will be phased out in 2025 the year after the completion of clinical surveillance. There are reasons to hope that at least some of the study households will continue enrolment in the insurance scheme after study completion.

### Dissemination policy: trial results and authorship

The study findings will be disseminated by publication in the peer-reviewed journals and presented in scientific conferences. The findings will be shared with the study participants’ community through community meetings and summary leaflets that will be provided to the village offices. The investigators will be involved in reviewing drafts of the manuscripts, abstracts, press releases, and any other publications arising from the study. Authorship will be determined in accordance with the ICMJE guidelines and other contributors will be acknowledged.

### Availability of data and materials: reproducible research

The study data will be available upon reasonable requests to the Mahidol Oxford Tropical Medicine Research Unit Data Access Committee (http://www.tropmedres.ac/data-sharing) for researchers and following the Mahidol Oxford Tropical Medicine Research Unit data access policy (http://www.tropmedres.ac/_asset/file/datasharing-policy-v1-1.pdf).

### Analytical plan

#### Incidence of malaria, respiratory tract infections, and diarrhoea diseases

Protective efficacy against clinical malaria, pneumonia, and diarrhoea diseases will be assessed by comparing incidence rates between the two study arms adopting an intention-to-treat analysis. Children within each household will be monitored using active and passive case detection throughout the study period. After treatment for malaria, the child will not be considered at risk for the following four weeks and this period will be censored. History of travel and nights spent away from the designated household will be captured during weekly surveillance visits and time at risk will be censored for such periods. Initial unadjusted analyses will be based on the comparison of the incidence rates between the two arms. Formal analyses will use a mixed effects Poisson model to test the difference in incidence rate between the two arms allowing for the repeated measurements within a house, a village and the effect of year using of confidence intervals that account for the highest level of clustering [28]. With multiple control and intervention houses within each village, the “intervention*village” interaction will also be quantified. Possible confounders such as age of child, gender, ethnicity, and rainfall will be tested using the mixed effects model. A mixed effects negative binomial model will be considered in case of overdispersion in the mixed effects Poisson model. A comparison of time to infection (both first and repeat) will be examined using a survival analysis approach. Initial analyses will be based on Kaplan-Meier curves with further adjustment for confounders performed using a Cox regression model.

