**Fig. 1 Fig1:**
[figure not shown]
Diagram illustrating the critical elements of the novel rural African house design

One of the requirements for a family to participate in the lottery for a house was to have space to build a new house. This building site on the land available to the future house owner was selected in discussion between the house owner and the architects taking into account any slope in the terrain and trees which can provide shade. The orientation of the building in relation to the north-south axis was determined by the architects. The ultimate position for the latrine was the result of the discussions between the house owners and the architects. Mosquito breeding sites of mosquitoes were not taken into consideration. Because the space available for construction was limited, the new house frequently replaced the earlier traditional home.

The construction of the 110 novel-design houses started at the end of 2018 and was completed in June 2021 when the houses were handed over to the new house owners. A maximum of three new houses were built in each village to minimize the risk of mosquito diversion, i.e. mosquitoes prevented from entering an intervention house being diverted to a control house and thus inflating malaria transmission in control houses. The residual mosquito diversion is unlikely to increase exposure in unprotected homes [19].

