### Randomization

All households meeting the eligibility criteria were invited to participate in a randomization process in the form of a village lottery. A total of 862 households were eligible to participate in a lottery to select firstly the 110 new house owners and secondly the 440 households to serve as comparison houses. The lottery was conducted during a public meeting at a central meeting place to which all villagers were invited. All households meeting the inclusion criteria were listed, and cards with the names of the household’s heads were inserted in identical envelopes. The envelopes were placed in a transparent bucket and mixed. The lottery consisted of two rounds where the winning envelope was picked by a literate school child of any age. In the first stage, two envelopes were picked out of the bucket, and the winners were offered a new house. During the second round of the lottery, eight households were randomly selected to participate in the study as comparison households. Comparison households will receive modifications of their homes such as a corrugate iron roof and water harvesting equipment after completion of the 3-year surveillance period. All study families, control and intervention, are enrolled in a health insurance scheme which assures free healthcare for the study duration. Each household meeting the eligibility criteria had an equal and fair chance of being selected to be part of the study (Fig. 2).

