### Sample size calculations

Our sample size estimates are based on malaria incidence in Korogwe, Tanzania, observed during the RTS,S cohort phase 3 trial [26]. Malaria epidemiology in Tanzania is quickly changing, and the main burden of disease has moved from young children aged 5–17 months to older children and adolescents. Assuming malaria episodes of 10/100 children/year in the control and a 30% reduction from 10 to 7 malaria episodes/100 children/year, a coefficient of variation (CV) of the outcome of 0.25, as recommended by Hayes and Moulton 2009 [27], detecting the difference in incidence rates with 80% power and testing at 5% significance level, we would need 105 clusters (households) with three child/years of observations per household per arm. To allow for loss to follow-up, we plan to recruit 110 households to the intervention arm. Since analysis requires adjustment for clustering by village and household [28], power simulations were performed using a random effects model to assess what ratio of traditional to novel-design households provides adequate power. For every intervention house, we will recruit four control houses, which will provide at least 80% power at the 5% level of significance to detect a 30% risk reduction. Since ICCs that accommodate village and household level clustering are rarely reported, we compensated for clustering from both levels by choosing a conservatively high ICC of 0.6. Because malaria is generally rarer than either respiratory diseases or diarrhoeal diseases in the study population, the sample size should suffice to measure a 30% reduction in all diseases under investigation at a 5% level of significance and 80% power. The sample size was performed in Stata 15 using the following basic command: clustersampsi, samplesize rates r1(.1) r2(.07) m(10) cluster cv(0.25) alpha(0.05) beta(0.8) base correl (0.6). The simulation results are shown in Fig. 4 below. Simulations were performed in Stata, and each scenario was simulated 5000 times and the empirical power was obtained. We considered 20, 40, 80, and 110 households in the intervention.

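### The time-to-infection analysis is stated without the household and village adjustment that the protocol requires, and it names Kaplan-Meier curves for an outcome that includes repeat infections

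*Protocol article*

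**What the plan says.** All references are to the protocol article.

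- **Sample size calculations.** The clustering requirement is general and not tied to one model: "Since analysis requires adjustment for clustering by village and household".
- **Analytical plan, incidence subsection, main test.** "Formal analyses will use a mixed effects Poisson model to test the difference in incidence rate between the two arms". House, village and year enter this model, and its intervals are to be formed "using of confidence intervals that account for the highest level of clustering". A negative binomial version is held in reserve for overdispersion.
- **Same subsection, crude comparison.** "Initial unadjusted analyses will be based on the comparison of the incidence rates between the two arms".
- **Same subsection, survival analysis.** "A comparison of time to infection (both first and repeat) will be examined using a survival analysis approach". The methods follow at once: "Initial analyses will be based on Kaplan-Meier curves with further adjustment for confounders performed using a Cox regression model". No village stratum, household frailty, robust variance or recurrent-event method is named.
- **Randomization.** "In the first stage, two envelopes were picked out of the bucket, and the winners were offered a new house". A second round then drew eight comparison households. The eligibility section gives 60 participating villages, and the study design section gives 110 and 440 houses.
- **Intervention, text after Fig. 1.** "A maximum of three new houses were built in each village".

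**The concern.** The household is the randomised unit and the village is the block. Each household contributes about three children, and each child can contribute several malaria episodes. Where the authors want dependence handled they say so: the Poisson model carries house and village, and the entomology analysis adjusts for repeated measures within houses. The survival analysis stands beside these and names adjustment for confounders only. An analyst working from this text would fit an ordinary Cox model, and its standard errors would ignore shared household risk and repeated events in one child.

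The outcome also includes repeat infections, while the first analysis named is Kaplan-Meier, which estimates the distribution of time to a single event. The plan removes four weeks of risk time after each malaria treatment and also removes nights away from home. Time at risk for later episodes is therefore broken into pieces, which a standard Kaplan-Meier curve does not represent.

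At stake is a hazard ratio reported next to the primary rate ratio with an interval that overstates its precision. It could look significant when the clustered Poisson result does not.

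**Working it through.** **1. Size of the household effect**

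Inputs:
- 110 and 440 households (study design).
- About 330 and 1320 children followed for 3 years (abstract). 330/110 = 3 and 1320/440 = 3 children per house, so 3 × 3 = 9 child-years per household.
- Control rate 0.10 per child-year and CV 0.25 with households as clusters (sample size section). CVs of 0.5 and 1.0 are assumptions.

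The log rate ratio under no effect is used as a stand-in for the log hazard ratio (constant hazard, all episodes counted).

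- Expected events: 110 × 9 × 0.10 = 99 and 440 × 9 × 0.10 = 396.
- Naive variance: 1/99 + 1/396 = 0.01263.
- Variance added by households: k² × (1/110 + 1/440) = k² × 0.01136.
- Ratio of true to naive variance: 1 + k² × 0.01136/0.01263 = 1 + 0.9k².
- True type I error of a nominal 5% test: 2 × [1 − Φ(1.96/√ratio)].

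| Household CV | Variance ratio | SE ratio | True type I error |
|---|---|---|---|
| 0.25 (protocol) | 1.056 | 1.03 | 5.7% |
| 0.5 (assumed) | 1.225 | 1.11 | 7.7% |
| 1.0 (assumed) | 1.900 | 1.38 | 15.5% |

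The sample size text writes three child-years per household. On that figure the ratio at CV 0.25 is 1 + 0.0625 × 0.10 × 3 = 1.019 and the type I error is about 5.2%.

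A simulation under no effect (20,000 runs per setting, nine child-years per house, 1:4 in every village, village CV from 0 to 1) gave naive type I error of 5.6–6.4% at household CV 0.25, 7.7–10.4% at 0.5 and 15.7–23.4% at 1.0. With village variation alone it was 4.8–4.9%. The inflation therefore arises from ignoring households, not from villages differing in risk.

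The table does not include extra variation between children in the same house, which would add to the dependence when repeat episodes are counted. An analysis of first infections only has fewer events per house, so its inflation would be somewhat smaller.

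**2. Lottery count**

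- As described: 60 × 2 = 120 and 60 × 8 = 480, total 600. Stated: 110 and 440, total 550.
- 110/60 = 1.83 houses per village, so the number of houses cannot have been the same in all 60 villages.
- The ratio can still be constant: 50 villages at 2:8 and 10 at 1:4 give 100 + 10 = 110 and 400 + 40 = 440.
- If those 10 villages have r times the risk of the others, the mean risk is (100 + 10r)/110 in the intervention arm and (400 + 40r)/440 in the control arm. The two are equal for every r, so the pooled ratio under no effect is 1.00.

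**The case against.** The strongest reply is that the article is condensed and never says the Cox model is unclustered. The statement in the sample size section can be read as governing every analysis, and the choice of frailty, robust variance or recurrent-event model is normally left to an analysis plan, which is not shown here. The formal test already models house and village, and both the crude rates and the Kaplan-Meier curves are labelled initial. At the protocol's own CV the inflation is under one percentage point.

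Much of this stands. The primary conclusion is not at risk, and the text does not prove that clustering will be ignored. But the paragraph spells out clustering for one model and, a few sentences later, names only confounder adjustment for another. It also names Kaplan-Meier for an outcome defined to include repeats. Time to a second infection can be plotted, but the text does not define such an endpoint. This wording needs correcting whatever the analysis plan adds.

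Two stronger readings are tempting, and the documents do not support them.

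- **Village confounding.** A reader might infer from the lottery numbers that pooled curves and crude rates are confounded by village. Unequal counts do not cause that; ratios that vary with village risk would. The totals are exactly 1:4, the sample size section plans four controls per intervention house, and the eligibility section seeks at least five households per village, which suits a 1:4 draw.
- **The intraclass correlation of 0.6.** Read as a household correlation with three children per house, it gives a design effect of 1 + 2 × 0.6 = 2.2 and a type I error of 18.6%. The protocol calls this value conservatively high and lets it cover both levels, and the quoted command enters it as a correlation beside a baseline option. It is not a usable estimate of sibling correlation.

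**Conclusion.** The point holds for the supplementary survival analysis only. As written, that analysis does not carry the household and village adjustment that the protocol says is required, and Kaplan-Meier is the wrong description for recurrent infections. The cost in type I error is small on the protocol's own assumption (about 5.7% instead of 5% at CV 0.25). It becomes material only if households differ more than that: 7.7% at CV 0.5 and 15.5% at CV 1.0, both assumed. These figures rest on nine child-years per household, a rate of 0.10, a constant hazard and a large-sample normal test.

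The mixed effects Poisson analysis of the primary endpoint is not affected. The lottery description conflicts with the stated arm sizes and needs reconciling, but it is a minor reporting item and not evidence of bias in the pooled comparisons.

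**What to change.** In the incidence subsection of the analytical plan:

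1. Stratify the Cox model, and any log-rank test, by village, the randomisation block.
2. Use household-clustered robust variance or a shared household frailty, and say which.
3. Restrict Kaplan-Meier curves to first infection.
4. For repeat infections, use an Andersen-Gill type model in counting-process form, which accommodates the excluded periods, and plot the mean cumulative function by arm.

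Separately, reconcile the two-plus-eight lottery description with 110 and 440 houses in 60 villages and with the maximum of three houses per village. Add a table of novel and comparison houses by village, so that readers can see whether 1:4 held throughout.

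The cost is a few sentences and a few lines of code, with no new data. Intervals for the hazard ratio become slightly wider: about 3% on the log scale at CV 0.25, and more only if household clustering is in fact stronger.

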#### Entomology (malaria transmission)

Differences in malaria transmission experienced in the two groups will be made by comparing the mean number of malaria mosquitoes (as a proxy for transmission) caught indoors in houses between the study arms. Generalized estimating equations will be used to estimate the differences in numbers of indoor-resting mosquitoes, adjusting for repeated measures within houses and possible covariates. We will compare the entomological inoculation rate in both arms. Human behavioural studies will also be carried out to compare when people move indoors and outdoors of the house, since the new housing intervention may change the way individuals use a house, which changes their exposure risk. Observers will record human movement including the age and gender of individuals with their identity anonymized.

#### Clinical (*P. falciparum*, respiratory infections, and diarrhoeal diseases)

*P. falciparum* prevalence in children will be estimated at the start of the transmission season through a cross-sectional survey. Falciparum malaria and respiratory and enteric disease incidence will be estimated based on active and passive surveillance and compared between the study arms. The incidence of all-cause febrile illness during the 3-year study and age-adjusted growth rates will be estimated in children under 5 years old.

#### Acceptability

Perceptions of the novel design house owners and the general community regarding the aesthetic appearance and convenience of the houses, use of different spaces in the house, its design elements, and construction materials will be summarized to provide an overall impression of acceptance of the novel design houses. The proportion of owners of control houses who choose to have home improvements at the end of the study will be determined.

#### ITN use

The proportion of children sleeping under ITNs between study arms at different times of the year will be compared.

#### Architectural

Indoor temperatures, humidity, CO_2_, and PM_2.5_ particle pollutions will be quantified using data loggers and compared between the two study arms. This will provide data regarding the level of air pollution between novel design and traditional homes and whether it correlates with respiratory tract infections. The durability of the novel design houses will be assessed by yearly inspections of houses. In traditional houses, maintenance records will be kept to allow comparisons between the study arms.

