### Social science

A mixed-method approach will be deployed for the assessment of acceptance and the use of each component of the novel design house (i.e. kitchen, storage area, bedroom, latrine, water collection facility). Data will be collected using focus group discussions (FGDs), in-depth interviews (IDIs), and a structured questionnaire-based survey at the beginning of the study and after 1 to 2 years. In-depth interviews will be conducted with approximately 18 selected heads of the households as well as selected members of the community (community leaders, health workers, religious leaders, etc.) to get their perspectives of the new house designs (design elements, construction materials, aesthetic appearance, etc.) and use of the house. FGDs will be conducted with a group of eight to 10 participants including respondents from both study arms and other selected members of the community to explore the community’s perception of the novel design houses. Approximately 10 FGDs will be conducted with approximately a total of 100 participants taking part in the discussions. The construction costs of novel design houses will be estimated and used to assess incremental costs and cost-effectiveness of the interventions.

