### Safety and adverse events

Since the intervention, a novel design house is no health or safety risk which could expose participants to harm neither a data safety monitoring board (DSMB) has been appointed nor is an interim analysis planned. It is not reasonable to anticipate that novel design houses which have been carefully planned with regard to safety features will lead to an increase in adverse events.

Study households are visited weekly by research assistants, and structural problems such as tears in the shade net used for screening, solar electricity supply, or water harvesting are addressed and repaired within days. In the unlikely case that the study team is alerted of a safety issue, the problem will be addressed immediately by our standby construction/repair team in charge of building maintenance.

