##### Durability

Yearly inspections of all study houses will be conducted to assess durability and modifications of the various components of the building structure.

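### Novel-house durability is to be judged by yearly inspection although faults are repaired within days, and repair records are named only for traditional houses, so the comparison would tend to overstate novel-house durability

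*Protocol article*

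**What the plan says.** Durability of the novel house's components is a secondary objective. The Abstract (Methods/study design) goes further and promises durability and cost-effectiveness of the new houses relative to traditional ones, so a between-arm comparison is intended.

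Two sections describe the measurement, and they differ:

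- Secondary endpoints, Durability: "Yearly inspections of all study houses will be conducted to assess durability and modifications of the various components of the building structure".
- Analytical plan, Architectural: "The durability of the novel design houses will be assessed by yearly inspections of houses. In traditional houses, maintenance records will be kept". The stated purpose of those records is a between-arm comparison.

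Safety and adverse events describes upkeep during follow-up. Every household receives a weekly visit from the field staff. On faults, the section states: "structural problems such as tears in the shade net used for screening, solar electricity supply, or water harvesting are addressed and repaired within days". It also mentions a standby team responsible for building maintenance. Ancillary and post-trial care says that house maintenance is free and will be phased out in 2025, after clinical surveillance ends.

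On cost, the Social science section says: "The construction costs of novel design houses will be estimated and used to assess incremental costs and cost-effectiveness of the interventions". The Economics endpoint names construction costs and cost benefits for both types of house. Neither place mentions upkeep.

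**The concern.** A torn screen, a failed solar supply or a broken rainwater system is a durability failure, whether or not someone mends it quickly. In this trial such faults are mended quickly, by the project. An inspection once a year then describes how well the houses are kept up, not how often their parts fail.

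The Architectural section adds a difference between arms. It gives the novel houses an inspection and the traditional houses a maintenance record, and says that this permits comparison. Repairs would then be visible in one arm and mostly invisible in the other.

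A durability result is at stake that readers may use when deciding what to build in places where no project repair team exists. The same gap touches the economic result. The health effect is measured in houses whose screening is kept intact at project expense, and the only cost named is the cost of building them.

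**Working it through.** The documents give no figure for durability or cost-effectiveness, so there is nothing to reproduce. The check sets the sections side by side and adds one illustration.

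**Which houses get which measure**

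| Measure | Novel houses | Traditional houses |
|---|---|---|
| Yearly inspection, Durability endpoint | yes | yes |
| Yearly inspection, Architectural | yes | not named |
| Maintenance record, Architectural | not named | yes |
| Weekly household visit, Safety | yes | yes |
| Rapid repair, Safety | examples are novel-house features | not stated |

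The Safety section's examples are shade net, solar supply and water harvesting. The Intervention section lists all three as parts of the novel house. The Randomization section gives comparison households water harvesting equipment only after the 3-year surveillance. The repairs described therefore fall mainly, perhaps wholly, on the novel houses. No section says that they are recorded or that they enter the durability result.

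**How much a yearly inspection would see**

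If faults arise evenly over the year and each stays open for d days, the chance that a fault is open on the yearly inspection day is d/365. The article says only that repair takes days, so d is an assumption:

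- d = 3: 3/365 = 0.8%
- d = 7: 7/365 = 1.9%
- d = 14: 14/365 = 3.8%

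A second route builds d from its parts. The mean wait for a weekly visit is 7/2 = 3.5 days. Adding an assumed 2 to 7 days for the repair gives d = 5.5 to 10.5 days, and 5.5/365 = 1.5% to 10.5/365 = 2.9%. The two ranges agree.

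In counts: if the 110 novel houses had one fault each in a year, the inspections would find 110 × 3/365 = 0.9 to 110 × 14/365 = 4.2 of those 110 faults still open.

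These shares concern faults still open. A patched net or a replaced part may be recognisable later, so the share leaving some evidence is higher, by an amount the documents do not give.

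**Direction**

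If traditional-house repairs are counted from records and novel-house repairs are not counted, the novel house looks more durable than it is. If both arms are judged by inspection alone, as the Durability endpoint would allow, the instrument is the same, but the novel houses are still seen after project repair.

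**Cost**

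The Social science and Economics sections name construction cost. They neither include nor exclude upkeep. Leaving out project-paid repairs would favour the novel house. Leaving out the upkeep of mud walls and thatch would work against it. No upkeep figure is given for either arm, so neither the net direction nor the size can be calculated.

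**The case against.** The strongest reply has four parts.

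- *The inspection is common to both arms and covers modifications.* This is what the Durability endpoint says, and it softens the point about different instruments. It does not bring repair events in the novel houses into the result, and it leaves the Architectural section saying something else.
- *Records kept to permit a comparison imply something comparable in the novel arm, and the repair team may well keep a log.* This is plausible. A reader might infer that no such log exists; a condensed article does not support that inference. What stands is that the article, where it fixes the measure for the novel houses, names inspection and not repairs.
- *The d/365 figure treats a mended fault as invisible.* The criticism is fair. The figure is the share still open, and it cannot be read as showing that all other faults leave no trace.
- *Naming construction cost does not exclude other costs.* This is correct. A reader might infer that cost-effectiveness will rest on construction cost alone and will therefore favour the novel house. The text supports neither step: the Economics endpoint adds cost benefits, costing detail may sit in the full protocol, and upkeep is unnamed for traditional houses too.

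The stated objective is also worded for the novel house alone. The Abstract and the Architectural section nevertheless both announce a comparison, and missed repairs would distort the novel-house result even without one.

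**Conclusion.** The durability point holds. As the Architectural section is written, novel-house durability rests on a yearly look at houses that the project repairs within days, and repair records are named only for the traditional arm. With faults open for an assumed 3 to 14 days and arising evenly, about 1-4% would still be open at inspection. The likely effect is to overstate novel-house durability relative to traditional houses. By how much depends on fault rates, visible traces of repair and any existing repair log, none of which the article gives.

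The cost point is secondary. Upkeep is not named as a cost, and the health effect is obtained in maintained houses. That justifies asking for upkeep to be counted in both arms, but it does not show that the economic result will lean towards the novel house. Both are secondary outcomes, and the primary malaria comparison is unaffected.

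**What to change.** 1. Reconcile the Durability endpoint with the Architectural section, so that both state which houses are inspected and which have maintenance records.
2. Keep the same repair record in both arms: date, component, fault, labour and materials, and who paid. The weekly household visits already reach both arms and can supply it.
3. Count repairs as durability events, for example faults per house-year and time to first repair, by component. Keep the yearly inspection as a supplement for wear and modifications.
4. In the economic analysis, state that upkeep is counted in both arms, including repairs paid for by the project. Showing the result with and without upkeep would let readers see what it contributes.

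The cost is some wording and a structured log, since visits and repairs already take place. If a repair log exists, only the wording and its use in the analysis change. If none exists, it should start soon, because unrecorded repairs may not be recoverable. Durability and cost-effectiveness may come out less favourable to the novel house.
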